### Recruitment

2.5

This study shall enroll patients with mild to moderate stroke as outlined by the inclusion and exclusion criterion set, to evaluate the efficacy of the AI-HEALS intervention. Recruitment shall be done by the hospital clinical team, which shall screen potential participants upon admission and provide them with the option of enrolling into the study. Subsequently, the study team shall conduct face-to-face consultations, which shall involve clarifying the study goals, procedures, potential benefits, and associated risks. Eligible patients shall be asked to receive a thorough health evaluation, involving discussion of the history of their stroke and current symptom. Only when there shall be complete understanding of the study, including clarification of all questions, shall patients be asked to provide an informed consent form. The participants shall only enroll into the study upon signing of the written informed consent form. Over the three-month AI-HEALS intervention, assessments will be conducted at baseline (pre-intervention), at discharge, at the end of the intervention, and during follow-up. To encourage maximum patient participation, all participants will receive a free medical consultation at the end of the study as an incentive for their participation.

### Informed consent

2.6

Informed consent process shall be carried out openly, transparently, strictly abiding by ethic values. Patients meeting inclusion, exclusion criteria shall be given a clear, detailed, written statement of the primary objectives of the study, special procedures, potential risks as well as benefits, including data protection available to them. It shall include all explanations of how their data shall be collected, stored, secured. All data shall be saved on secure, encrypted format on specially guarded servers, readable only by authorized personnel of the research team once they are on the study, disposed of properly at study completion.

Participants will have sufficient time to read the informed consent form, pose questions, and willingly offer their written consent. They will fully be made aware of the privilege of withdrawing from the study at whatever time without adverse effects on them. The research team will offer sustained contact details to ensure that participants may, at whatever time, request further clarification or help. During the study, new information that may influence participants’ motivation to continue will, at once, be revealed, hence preserving ongoing informed consent throughout the study.

Moreover, participants will incur no penalty for choosing to withdraw from the intervention group. If the intervention has already begun, patients choosing to withdraw will never be transferred into the control group but are retained as dropouts. Semi-structured interviews, as far as possible, shall be conducted on such persons regarding reasons for terminating. During consent, participants shall be specifically informed of all post-withdrawal decisions such that at all steps they remain fully aware of decisions as well as rights of theirs that persist over time of study.

### Intervention

2.7

#### Control group: standard care group

2.7.1

The participants assigned to the control arm shall receive standard care offered by a multidisciplinary clinical team. Such standard care shall include the following: Regular visits to physicians for ongoing assessment of well-being and refinement of treatment; Scheduled follow-up visits to evaluate disease progression; Systematic diagnostic tests to screen selected health indicators; Carried out structured education on health on managing diseases, treatment adherence, and lifestyle changes.

#### Intervention group: standard care + AI-HEALS

2.7.2

Participants of the intervention group shall receive standard care and a three-month AI-HEALS intervention from the WeChat service platform “Stroke Health Management Expert.” The intervention team is composed of public health professionals, physicians, clinical nurses, psychologists, and statisticians, each contributing their specialized expertise to the design and implementation of the intervention. The program consists of the following four core program elements:

Knowledge-Based Question Answering System on Stroke (KBQA): This module would enable patient education on stroke issues through an intelligent FAQ chatbot (FAQRobot), such that patients obtain accurate and efficient knowledge on stroke. To achieve the same, a deep and credible knowledge base shall be built, covering a wide topic spectrum including basic concepts, etiology, symptom, treatment, medication regimen, day-to-day control measures, healthy diet, and proper exercise. The knowledge base shall be incorporated into the Doubao Large Language Model (developed at ByteDance), such that the system would provide accurate, professional answers to patient questions fed through the WeChat messaging channel. To enhance interactivity and user engagement, the system will suggest three related follow-up questions based on each user query, encouraging patients to explore relevant content in greater depth. Voice-interaction capability is also provided, allowing patients to ask stroke-related questions through voice input. To continuously optimize the knowledge base and make user experience richer, the system would record patient questions and usage behavior (e.g., frequency of visits, time spent on the site) through backend monitoring, which would be analyzed to understand user behavior patterns. Such data shall further influence updating of knowledge base and question-answering system on a continuous basis, ensuring that the knowledge provided remains relevant, accurate, and up-to-date.Recording and Monitoring of Physiological Indicators and Lifestyle Changes: Participants will be asked to regularly record some of their lifestyle-linked data through the AI-HEALS system, e.g., food patterns, exercise, and medication adherence. These data will be entered into electronic form and uploaded into the system, which will allow research staff at all times to observe continuously patients’ self-management activities over time as well as changes over time for every patient. Such data analysis, and data collection, will make possible not only evaluation of the impact of the intervention on patients’ day-to-day activities but also optimization of person-centered treatment plans, thereby enhancing the overall effectiveness of health management.Personalized Reminder Services: To support treatment compliance, the AI-HEALS system provides customizable reminder functions. Patients can voluntarily set personalized alarms and the system will deliver reminders only at the times selected by the user. For example, medication schedules or monitoring tasks importantly. Additionally, participants may adjust the frequency of reminders or disable them at any time within the system, ensuring that the feature remains fully user-controlled and minimizes unnecessary burden.Automated and Personalized Stroke Self-Management Information: This study incorporates a kind of automated provision of information system through which participants will receive at the same time 1 to 3 informative messages each week on stroke self-management. The contents of such messages are proper diet suggestions, exercise guidelines, as well as medication concerns. What the researchers envision is patients’ health literacy improvement and people’s promotion toward utilizing enhanced self-care practices on a day-to-day basis. Additionally, the system through participants’ interacting chatbot data will intelligently provide sharper educative content that relates to particular needs. In order to optimize even further the outcomes of provision of information, the researchers at their side continuously evaluate backend data, including the number of articles, article types, and article reading time, each participant has progressed through. Relating to such outcomes, the content and provision frequency of the system will continuously change to make them more relevant, accurate, as well as efficient.

The “Doubao Pro-32 k” large language model (LLM) used here has been a Chinese-trained transformer-based model specifically optimized for uses of medical knowledge. It has received training on a combination of biomedical literature along with stroke-specific clinical guidelines and fine-tuned on a 32 k context window to facilitate the production of long-form health education content. Prior to domain-specific fine-tuning, pretraining of the model had covered extensively general language understanding to support its capabilities of performing medical reasoning. It had its performance evaluated on the third-party FlagEval evaluation platform,^1^ on which it demonstrated competitive performance against GPT-4.0. Doubao Pro-32 k had achieved an aggregate score of 77.75, significantly outstripping GPT-4.0’s 73.51 score. Most importantly, its best performance was on the domain of knowledge application, where it achieved 91.14, as opposed to GPT-4.0’s 86.71—a particularly crucial competency to create evidence-based clinical information. Following development, the model’s output had garnered initial expert assessment to make it aligned with prevailing knowledge of medicine and meet rigorous requirements needed for purposes of clinical research studies. Furthermore, at the close of the pilot RCT, a continuous validation process shall be established. As part of the process, two experts shall, on a monthly basis, assess 10% of the model’s output through assessing its appropriateness and ensure the system’s sustained reliability as well as integrity.

Finally, protecting participant privacy and ensuring data security during interactions with the AI-HEALS system are priorities. All patient information gathered for the research study will be kept confidential and encrypted, and no personally identifiable information would be submitted to WeChat. Participants are free to withdraw their participation from the research study for any reasons they prefer and without penalty. In order for AI-produced content to be utilized correctly, the knowledge base of the system and the accuracy of the AI responses are carefully checked and revised by healthcare professionals. This ensures that the information produced by AI remains valid and that research study participants are not exposed to incorrect information.

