Mobile health (mHealth) and artificial intelligence (AI) technologies have simplified personalized and continuous support for people living with chronic conditions. mHealth applications provide distant access to health information, reminders, and patient self-check facilities. AI can improve such applications by allowing for response generation, tailored content, and proper use of patient-submitted information. These concepts assist patients to stay engaged and simplify their overall self-management. For the purpose, the Artificial Intelligence Health Education Accurately Linking System (AI-HEALS) was designed as a WeChat-based tool for complementing the conventional rehabilitation process for patients with mild to moderate stroke. AI-HEALS incorporates proven behavioral model concepts, the Health Action Process Approach (HAPA) and the Multi-Theory Model (MTM) (18, 19), to direct the design of the education and behavioral components. AI-HEALS consists of the following functional elements: an AI-supported question-and-answer section with an organized and updated knowledge base, the capacity for the recording of healthcare and behavioral information, reminders, and health education. Though named AI-HEALS, the system actually serves as an AI-driven health education and management system and not as therapy. This tool would assist patients in managing their health outside the healthcare environment.

Based on it, this protocol describes a single-blind, randomized controlled trial (RCT) designed to systematically evaluate the effectiveness of the AI-HEALS in promoting self-health management among patients with mild to moderate stroke. The specific objectives of the study are:

To determine whether a 3-month AI-HEALS–based comprehensive intervention improves physiological indicators, including blood pressure, blood glucose, and body weight;To assess the intervention’s impact on psychological outcomes, such as anxiety, depression, and self-efficacy;To evaluate the effectiveness of the intervention in enhancing self-management behaviors, including medication adherence, engagement in rehabilitation exercises, and healthy dietary practices.

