##### Self-management behaviors

2.9.2.1

Changes in self-management behaviors will be assessed across multiple domains, including: behavioral decision-making, nutrition preference, physical activity, medication adherence, smoking and alcohol control, sleep patterns, quality of life, functional autonomy in daily living.

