##### Psychosocial and cognitive measures

2.9.2.2

These include: perceived recurrence/stroke risk, health literacy, self-efficacy, depression, anxiety, stress, perceived social support. These outcomes evaluate psychological and behavioral dimensions associated with secondary stroke prevention.

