### Variable measurement

2.10

Sociodemographic measures will be obtained at baseline. Physical examinations and questionnaire evaluation are scheduled at the following time points: baseline, at hospital discharge, at the end of the intervention, and at 3, 6, and 9 months post-intervention (Table 1).

**Table 1 tab1:** The schedule of enrolment, interventions, and assessments.

Study period	Recruitment	Intervention		Follow-up		
Timepoint	0	Discharge	3 Months	3 Months	6 Months	9 Months
Eligibility screen	✓					
Informed consent	✓					
Allocation	✓					
Sociodemographic variables	✓					
RRPS-SP	✓	✓	✓	✓	✓	✓
BDMS-SP	✓	✓	✓	✓	✓	✓
PHQ4	✓	✓	✓	✓	✓	✓
PSSS-SF	✓	✓	✓	✓	✓	✓
NGSES-SF	✓	✓	✓	✓	✓	✓
EQ-5D-5L	✓		✓	✓	✓	✓
Smoking	✓		✓	✓	✓	✓
Alcohol consumption	✓		✓	✓	✓	✓
B-PSQI	✓		✓	✓	✓	✓
FCS-SF	✓					
eHEALS	✓					

BDMS-SP, the Behavioral Decision-Making Scale for Stroke Patients; B-PSQI, The new Brief Version of the Pittsburgh Sleep Quality Index-Short Form; eHEALS, The eHealth Literacy Scale; FCS-SF, The Family Communication Scale-Short Form; EQ-5D-5L, EuroQol-5 Dimensions 5 Levels; PHQ-4, the abbreviated Patient Health Questionnaire-4; PSSS-SF, The Perceived Social Support Scale; NGSES-SF, The New General Self-Efficacy Scale-Short Form; RRPS-SP, Recurrence Risk Perception Scale for Patients with Stroke.

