#### Anthropometric variables

2.10.2

Height, weight, waist circumference, and blood pressure of each participant shall once be measured through certified equipment for accurate measurements. Height and weight shall once be obtained through duly calibrated and certified electronic weighing scales. BMI shall once be calculated as weight in kilograms divided by the square of the height in meters. Waist circumference once shall once be obtained at umbilical level through the use of a measuring tape. Blood pressure, including both systolic and diastolic measurements, will be obtained once using a validated automated sphygmomanometer (24). Venous blood samples were collected during hospitalization and at follow-up visits. Glycated hemoglobin (HbA1c) was measured to reflect the average blood glucose concentration over the preceding 2–3 months, providing an indicator of long-term glycemic control (25). Lipid profiles included total cholesterol (TC), triglycerides (TG), high-density lipoprotein cholesterol (HDL-C), and low-density lipoprotein cholesterol (LDL-C) (26). Serum TC and TG were measured using enzymatic methods, which employ specific enzyme reactions to convert target lipid components into detectable products, offering high sensitivity and specificity (26). Serum HDL-C and LDL-C were determined using homogeneous assays, in which specific chemical reactions uniformly disperse lipoproteins to enable quantification of cholesterol in each fraction (26).

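### Five of the 15 secondary outcomes, including the three behaviours named in Objective 3, have no stated post-baseline measure in both arms

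*Protocol article*

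**What the plan says.** The third objective in the Introduction is: "To evaluate the effectiveness of the intervention in enhancing self-management behaviors, including medication adherence, engagement in rehabilitation exercises, and healthy dietary practices". Section 2.9.2.1 lists the self-management outcomes as "behavioral decision-making, nutrition preference, physical activity, medication adherence, smoking and alcohol control, sleep patterns, quality of life, functional autonomy in daily living". Section 2.9.2.2 lists the psychosocial and cognitive outcomes as "perceived recurrence/stroke risk, health literacy, self-efficacy, depression, anxiety, stress, perceived social support".

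On data capture, section 2.7.2 describes a recording module within the intervention: "Participants will be asked to regularly record some of their lifestyle-linked data through the AI-HEALS system, e.g., food patterns, exercise, and medication adherence". It adds that these records will serve, among other uses, to evaluate what the intervention does to patients' daily activities. Section 2.7.1 gives the control arm standard care only, and its list of components contains no such log.

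Table 1, titled "The schedule of enrolment, interventions, and assessments", has rows for 11 questionnaires. Section 2.10.4 describes the same 11. Table 1 ticks eHEALS at time 0 and at no later visit.

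**The concern.** A randomised comparison needs the outcome from both arms, at a time after treatment has begun. A log kept inside the intervention gives data from one arm only. It also has no stated pre-intervention value, and because the regimen lasts three months, no stated value at the 3-, 6- and 9-month follow-ups. It is entered by unblinded participants, whereas section 2.2 promises outcome data from research assistants blinded to allocation. A scale given only at baseline cannot show change or a treatment difference.

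Pilot status does not remove the problem. Section 2.4 wants feasibility parameters and preliminary effect sizes for planning a larger trial. For outcomes never collected from controls or after baseline, the pilot supplies no between-arm estimate and does not test whether they can be collected. Multiple imputation (section 2.11) cannot supply data that were never scheduled.

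**Working it through.** No figure in the plan needs reproducing; the check is a cross-tabulation. Each outcome in sections 2.9.2.1 and 2.9.2.2 was matched to an instrument in section 2.10 and to the ticks in Table 1.

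| Secondary outcome | Stated measure | Both arms, after baseline? |
|---|---|---|
| Behavioural decision-making | BDMS-SP | yes |
| Nutrition preference | AI-HEALS log only | no |
| Physical activity | AI-HEALS log only | no |
| Medication adherence | AI-HEALS log only | no |
| Smoking and alcohol | two questionnaires | yes |
| Sleep | B-PSQI | yes |
| Quality of life | EQ-5D-5L | yes |
| Functional autonomy | some EQ-5D-5L items | in part |
| Recurrence risk perception | RRPS-SP | yes |
| Health literacy | eHEALS, time 0 only | no |
| Self-efficacy | NGSES-SF | yes |
| Depression | PHQ-4 | yes |
| Anxiety | PHQ-4 | yes |
| Stress | none | no |
| Social support | PSSS-SF | yes |

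**Count.** Listed outcomes: 8 + 7 = 15. Fully measured: 9. Measured in part: 1. Not measured in both arms after baseline: 15 − 9 − 1 = 5, which is one third.

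**Could a scheduled scale cover a gap?**

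- BDMS-SP has four dimensions (10 + 9 + 5 + 6 = 30 items): motivation, intention, determinants and decisional balance. None records what a patient eats, how much they exercise or whether they take their medication.
- PHQ-4 has two depression items and two anxiety items, so no item is left for stress.
- EQ-5D-5L includes mobility, self-care and usual activities. It is scheduled at baseline, the end of intervention and all three follow-ups, so it gives a partial measure of functional autonomy. The article assigns it to quality of life.

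**Objective 3.** Its three named behaviours correspond to nutrition preference, physical activity and medication adherence in section 2.9.2.1. None of the three has a stated control-arm measure. Of the 8 self-management domains, 4 are measured in both arms (decision-making, smoking and alcohol, sleep, quality of life), 1 in part and 3 not: 4 + 1 + 3 = 8.

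**Health literacy.** Section 2.7.2 gives better health literacy as an aim of the weekly messages, and section 2.9.2.2 makes it an outcome. The baseline-only tick in Table 1 contradicts both.

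**The case against.** The strongest reply is that much of this is silence in a condensed article. Table 1 is plainly not exhaustive: it omits blood pressure, HbA1c and lipids, which bear on the primary outcomes. Sections 2.2, 2.11 and 3 refer to blinded assessors, structured questionnaires and validated questionnaires at standard times in both arms. No sentence makes the AI-HEALS log the source of the secondary outcomes. A full protocol may name the missing instruments.

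Part of this stands. A missing row in Table 1 is weak evidence by itself, and for stress the point does rest on silence. But section 2.10.2 describes the blood pressure and laboratory measurements that Table 1 omits, whereas diet, exercise and adherence appear nowhere in section 2.10. Section 2.10.4 and Table 1 agree one for one on 11 questionnaires, most with item counts and score ranges, so ordinary condensation is an unlikely explanation. Two of the problems are positive statements: eHEALS is scheduled at baseline only, and the one-arm log is said to allow evaluation of impact.

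A reader might infer more than the text supports:

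- *Objective 3 cannot be answered at all.* Its wording introduces the three behaviours as examples, and four other self-management domains are measured in both arms.
- *Six of 15 outcomes are unmeasured.* That count gives EQ-5D-5L no credit for functional autonomy.
- *Family communication is an outcome measured only at baseline.* FCS-SF is baseline only, but section 2.9 does not list family communication as an outcome. The Discussion speaks of family involvement, which is a different construct.
- *Blood pressure is taken only one time in the trial.* Section 2.10.2 says it "will be obtained once using a validated automated sphygmomanometer", but section 2.9.1 fixes six occasions, so the natural reading is once per visit. Any claimed gain from averaging readings would need standard deviations that the article does not give.

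**Conclusion.** The point holds for five of the 15 secondary outcomes: nutrition, physical activity, medication adherence, health literacy and stress. Followed as written, the trial yields no between-arm, post-baseline estimate for any of them. Functional autonomy is covered in part.

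Confidence is highest for health literacy, where the article contradicts itself. It is high for the three behaviours, whose only stated record is in a module that controls do not receive. It is lowest for stress, where a full protocol might name a scale. The conclusion assumes that controls have no access to the recording module, as sections 2.7.1 and 2.7.2 imply, and that section 2.10.4 is the complete questionnaire set.

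No primary outcome is affected, and section 2.4 puts feasibility ahead of efficacy. This should be fixed, but it does not undermine the trial as a whole.

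**What to change.** 1. Repeat eHEALS (5 items) in both arms at the end of intervention and at follow-up.
2. Add short medication-adherence, exercise and diet questionnaires to Table 1 and section 2.10.4, in both arms, at baseline, the end of intervention and follow-up, collected by the blinded research assistants.
3. State that the AI-HEALS logs are process data and will not be used to estimate the effect of the intervention.
4. Add a stress measure in both arms, or delete stress as an outcome.
5. Name the EQ-5D-5L items that serve as the functional-autonomy measure, or delete that outcome.

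The cost is a few minutes of questionnaire time at visits already scheduled, plus an amendment to Table 1 and section 2.10. Participants already enrolled may lack baseline values on the new scales. Their post-baseline values can still be compared between arms, but without baseline adjustment.

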## Study management

3

The Data Monitoring Committee (DMC) would consist of no less than two members of the Ethics Committee of the Luoyang First People’s Hospital. None of the members would have any conflict of interest regarding the research. The members would monitor the progress of the research study periodically and inform the Ethics Committee. They would not be involved in the research. In the case of unapproved changes to the research, the members of the DMC would recommend the termination of the research. Although AI-HEALS is a behavioral and mobile health–based intervention, similar mHealth or AI-assisted self-management programs have generally demonstrated a strong safety profile, with few or no serious adverse events (AEs) reported. Expected adverse events (if any) are expected to be minimal and non-physiological in nature, such as frustration when using technological devices, increased psychological burden caused by frequent reminders, or inconvenience during system interaction. No direct biomedical risks are expected, as the intervention does not involve pharmacologic, device-based, or invasive procedures. In the case of any AEs and serious AEs occurring to the participant, it would be communicated to the principal investigators within 24 h, and the study would be paused for further check. In case of major technical failure of the AI system and serious problems that might pose risks to the participants, as well as any issues regarding the user interface, the study would be halted immediately. Repairs would be conducted by the technical team. After the system had been repaired and stability had been confirmed, the study could either be reframed and continued if it was safe and sound scientifically.

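### The only specified audit of chatbot answers starts when the pilot closes, after participants' exposure, so the assurance that they meet no incorrect information is not supported

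*Protocol article*

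**What the plan says.** Section 2.7.2 of the protocol article describes three checks on the chatbot's content.

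- **Before the trial:** "Following development, the model’s output had garnered initial expert assessment to make it aligned with prevailing knowledge of medicine".
- **At the end of the trial:** "at the close of the pilot RCT, a continuous validation process shall be established". Within that process, "two experts shall, on a monthly basis, assess 10% of the model’s output through assessing its appropriateness".
- **No stated timing:** in the paragraph on privacy and data security, "the accuracy of the AI responses are carefully checked and revised by healthcare professionals". The assurance follows directly from this check: "research study participants are not exposed to incorrect information".

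The same section says that logged questions and usage feed back into the system: "Such data shall further influence updating of knowledge base and question-answering system on a continuous basis". It also sets the length of exposure: "Participants of the intervention group shall receive standard care and a three-month AI-HEALS intervention".

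Section 2.4 identifies this trial as the pilot that precedes a larger powered trial. Section 3 adds reporting of adverse events within 24 hours with a pause of the study, a halt for serious problems that might put participants at risk, and periodic review by the Data Monitoring Committee (DMC).

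**The concern.** A reader of Section 2.7.2 would expect the quantified audit to watch the answers that trial participants receive. As worded, it starts when there are no trial answers left to watch. The assessment made after development does not fill the gap, because the system it examined is then revised on a continuing basis.

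Two things are at stake.

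- **Safety oversight.** The knowledge base covers treatment and medication, and the users have been admitted with acute stroke. Section 3 states "No direct biomedical risks are expected" and gives technology frustration, reminder burden and inconvenience as examples of expected adverse events. Incorrect advice is not among them. An absolute assurance in Section 2.7.2 makes it less likely that anyone looks for it.
- **What the pilot teaches.** Section 2.4 makes feasibility the main purpose. Answer accuracy is not among the process indicators in Section 2.9.3 or the feasibility and system-use measures in Section 2.11. With the audit placed after the trial, the pilot has no planned estimate of accuracy from its own use.

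**Working it through.** The plan states no figure for audit coverage, so there is none to reproduce. The check is a comparison of timelines.

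**Inputs from the documents**
- Intervention participants: 30 (Section 2.4)
- Exposure: 3 months each (Section 2.7.2)
- Recruitment: February 2025 to February 2026, taken as 12 months (Section 2.3)
- Last follow-up: 9 months after the intervention ends (Section 2.9.1)
- Audit fraction: 10% of output (Section 2.7.2)

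**Assumptions:** even enrolment over the 12 months, no dropout, and output proportional to time on the system.

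**Total exposure:** 30 × 3 = 90 participant-months.

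**Overlap with the audit, by the meaning given to the close of the trial**

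| Audit starts at | Month | Exposure overlapped | Output sampled |
|---|---|---|---|
| End of last follow-up | 12 + 3 + 9 = 24 | 0 of 90 | 0% |
| End of last intervention | 12 + 3 = 15 | 0 of 90 | 0% |
| End of recruitment | 12 | 11.25 of 90 (12.5%) | 0.10 × 12.5% = 1.25% |
| First participant access | 0 | 90 of 90 | 10% |

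Third row: participants enrolled in months 9 to 12 are 3/12 × 30 = 7.5. Their mean remaining exposure at month 12 is 1.5 months, and 7.5 × 1.5 = 11.25. This is a stretched meaning of close and is shown only as a bound.

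**What the assurance would need.** Even in the last row, 100% − 10% = 90% of answers are not sampled, and a monthly review sees an answer only after it has been sent. Moving the audit gives detection and an error estimate. It cannot by itself show that nobody met incorrect information.

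**Illustration of what an in-trial audit could detect.** Usage and error rates are not in the documents, so both are assumed. P(at least one error found) = 1 − (1 − e)^m, where e is the error rate and m the number of answers audited. Reviewers are assumed to recognise every sampled error.

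| Assumed use per person | Answers | Audited (m) | Errors at e = 1% to 2% | Errors expected in the sample | P(at least one found) |
|---|---|---|---|---|---|
| One a day, 90 days | 30 × 90 = 2,700 | 270 | 27 to 54 | 2.7 to 5.4 | 93.4% to 99.6% |
| One a week, 13 weeks | 30 × 13 = 390 | 39 | about 4 to 8 | 0.4 to 0.8 | 32% to 55% |

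An in-trial audit could therefore be informative with heavy use and weak with light use. The timing point does not depend on this table.

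**The case against.** The strongest case on the other side has four parts.

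- **Other safeguards operate during the trial.** A reader might infer from the audit's timing that safety is unmonitored or that wrong answers go undetected. The documents do not support that. Section 2.7.2 says professionals check and revise the responses, and the assurance rests on that check rather than on the audit. Section 3 has adverse-event reporting, a halt rule and DMC review, and harm following a wrong answer would fall under its adverse-event reporting. Section 2.8 adds weekly monitoring, though of system use rather than answer accuracy. All of this stands. What remains is that none of these is described as reviewing a live answer before delivery.
- **A condensed article may leave the review procedure to the full protocol.** This also stands: the missing schedule for the professionals' check is not a finding. The start of the audit and the absolute assurance are different, because the article states both.
- **The wording may be a slip, or stored trial logs may be reviewed later.** Either is possible. If it is a slip, the text still needs correcting. The article does not say that the 10% sample would be drawn from stored trial answers, and a later review could not prevent exposure.
- **A monthly 10% audit is itself retrospective.** True. Bringing it forward therefore does not rescue the assurance, which has to be reworded in any case.

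**Conclusion.** The point holds in a limited form. On the plain reading, the only audit with stated reviewers, frequency and fraction covers 0% of the trial's 90 intervention participant-months. On the most generous reading, about 1.25% of output would be sampled. The zero needs only that the audit starts after the last participant's three months. The 1.25% also rests on even enrolment and on output proportional to exposure. The unqualified statement about incorrect information is not supported by the checks described, and would not be even with the audit running throughout.

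A reader might also take the illustrative 27 to 54 errors as the number of wrong answers that go unseen. That does not follow. The figure depends on assumed use and error rates, falls to about 4 to 8 at one question a week, and would require the professionals' check to find nothing.

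The change is worth making: it is cheap and improves both safety oversight and the pilot's feasibility information.

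**What to change.** 1. In Section 2.7.2, start the validation process *from first participant access and throughout the intervention*, in place of the close of the pilot. Keep the two experts, the 10% sample and the monthly cycle.
2. Report the observed error rate descriptively with the feasibility results, and pass clinically relevant errors to the DMC described in Section 3.
3. Replace the absolute assurance with a statement that the checks reduce the risk of incorrect information.

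Re-auditing after each knowledge-base update is an optional extra.

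Cost: the experts' monthly time falls within the trial period. The reviewers, sample and cycle are those already planned.
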